## Abstract

**Background:**

Laparoscopic appendectomy has progressively gained acceptance as the standard of care for acute appendicitis. Focusing on the incidence of postoperative intra-abdominal abscess after a laparoscopic appendectomy, discordant data have been reported ranging from 1.5 to 20%. Besides, evidence advocating advantages from peritoneal irrigation over suction only are lacking. Most studies are burdened by a high level of heterogeneity regarding the severity of the appendicitis and modalities of peritoneal irrigation. One of the main drawbacks is the lack of an accepted classification for different degrees of appendicitis and peritoneal contamination. The aim of the study is to introduce a classification to clarify the relationship between grade of appendicitis, contamination, and postoperative incidence of IAA considering the surgeon’s attitude toward irrigation or suction alone. Preoperative, intra-operative, and postoperative predictive factors for infectious complication will also be assessed. This study is meant to be the first Italian multicenter resident-based observational study.

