## Hypothesis, design of the study, and aims

The driving hypothesis of our study is that there should exist a relationship between different intra-operative treatment protocols (irrigation vs suction alone) and postoperative incidence of IAA. Furthermore, considering various grades of appendicitis and peritoneal contamination, the use of irrigation vs suction alone could lead to different rates of postoperative IAA.

The aim of this study is to introduce and evaluate a classification for acute appendicitis taking into account the peritoneal contamination to delineate the relationship between grade of appendicitis and postoperative incidence of IAA considering the surgeon’s attitude toward irrigation or suction alone. Some studies described that the incidence of postoperative IAA is higher in the perforated appendix [12, 13]. No clear evidence exists exploring the severity of peritonitis as a potential predictor of IAA and its relationship with irrigation or suction alone.

This is a prospective observational multicenter study.

Primary endpoint:Relationship among each severity grade of acute appendicitis and postoperative incidence of intra-abdominal abscesses

Secondary endpoint:Impact of intraperitoneal irrigation or suction alone on the incidence of IAA for each severity grade

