### Data collection and statistical analysis

Participants will fill an online form reporting all clinical and intra-operative data of each patient who will undergo a laparoscopic appendectomy. All personal information of patients will be removed according to data anonymization.

Data will be reported in accordance with Strengthening the Reporting of Observational studies in Epidemiology guidelines (STROBE) for observational studies [22].

Residents from each involved center will be responsible for data collection.

All forms will be collected in an electronic database by the coordinating residents who will check for data completeness. All residents taking part in the study will be asked to enter eventual missing data.

The incidence of IAA after laparoscopic appendectomy reported in the literature ranges from 1.5 to 20% [4, 5, 9–11]. Such a wide interval is not negligible when calculating the sample size (*n*) of the study cohort. Furthermore, some important basic considerations need to be taken into account: appendicitis is the most common acute surgical disease so the baseline population is large and cannot be exactly estimated; the incidence of intra-abdominal abscesses has never been systematically investigated in regard to the severity of appendicitis and contamination. All patients included in the study will be classified into different clusters considering the grade of appendicitis and contamination, lavage vs suction alone, and postoperative incidence of IAA.

Considering all these aspects, sample size for power calculation can be reasonably estimated given a 95% confidence interval with a *z*-score of 1.96, a 50% standard deviation, and a 0.03 margin of error. This formula does not include the incidence rate of IAA for the aforementioned reasons.

The estimated sample size would be around at least 1067 patients. Data will be collected in a computerized spreadsheet (Microsoft Excel 2016; Microsoft Corporation, Redmond; WA) and analyzed with statistical software (IBM Corp. Released 2017. IBM SPSS Statistics for Windows, version 25.0. Armonk, NY).

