*χ*^*2*^ test will be assessed to compare categorical variables, and univariate logistic regression will be performed to provide hazard ratios for individual variables, identifying possible predictors of postoperative complication (IAA above all). All significant (*p* < 0.05) variables at univariate analysis will be included in a multivariate regression model in order to detect independent risk factors for the outcome and to estimate odds ratio and 95% confidence intervals.

A scoring system will be built according to the results of statistical analysis. The weight of each variable will be addressed based on odds ratio values. To evaluate the accuracy of the score, discrimination and calibration of the model will be explored. The former will be assessed by receiver operating characteristic (ROC) curve analysis, whereas the latter will be investigated with the Hosmer-Lemeshow goodness-of-fit test. Based on the results of the ROC curve analysis, we will proceed to identify different severity grades of acute appendicitis each one related to a specific risk of developing delayed IAA. *χ*^*2*^ test will be assessed to compare categorical variables, and univariate logistic regression will be performed to provide hazard ratios for individual variables, identifying possible predictors of postoperative complication (IAA above all). All significant (*p* < 0.05) variables at univariate analysis will be included in a multivariate regression model in order to detect independent risk factors for the outcome and to estimate odds ratio and 95% confidence intervals.

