## Conclusions

The study proposed within this protocol may have different scientific, operative, and prognostic implications. The classification and the scoring system can be fundamental instruments for general emergency surgeon to identify various grades of appendiceal inflammation and peri-appendiceal contamination related to different incidence of postoperative infectious complications considering the use of irrigation or suction alone.

Thus, these instruments can be helpful to reduce selection biases and select homogenous cohorts of patients. The main scientific target should be planning and conducting well-structured studies to reach maximal external validity.

On the other hand, the biggest practical consequence from the application of the score can be the identification of intra-operative scenarios in which the impact of irrigation or suction alone has been clearly outlined. More awareness of the impact of daily surgical practices can help young and trained surgeons during daily surgical practice.

Surgical decision-making should be supported by solid evidence, especially in an emergency surgery setting. If particular aspects of surgical approaches are not adequately supported by clear data, the emergency surgeon cannot be completely satisfied by relying on common sense alone. Nowadays, maximum effort should be made to reach the best procedural standardization, especially during acute care procedures.

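### The univariate p<0.05 entry rule has no timing limit and no forced-in variable, so applied as written it can admit consequences of the abscess and drop irrigation

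*Protocol article*

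**What the plan says.** In *Data collection and statistical analysis*, each variable is tested alone, and all those significant at p<0.05 go forward: these "variables at univariate analysis will be included in a multivariate regression model in order to detect independent risk factors for the outcome". The sentence appears twice. The same section builds the score from that model ("The weight of each variable will be addressed based on odds ratio values"), judges it by ROC analysis, and takes the severity grades from the ROC result.

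No sentence limits candidates to what is known by the end of surgery, and none keeps severity, contamination or irrigation in the model. The Abstract points the other way on timing: "Preoperative, intra-operative, and postoperative predictive factors for infectious complication will also be assessed". The postoperative list in *Methods* includes length of stay, ICU stay, antibiotic duration, Clavien-Dindo grade, organ/space infection and emergency return with a diagnosis of IAA.

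The primary endpoint is "Relationship among each severity grade of acute appendicitis and postoperative incidence of intra-abdominal abscesses". The secondary endpoint is "Impact of intraperitoneal irrigation or suction alone on the incidence of IAA for each severity grade". *Conclusions* names as the main practical gain the "identification of intra-operative scenarios in which the impact of irrigation or suction alone has been clearly outlined".

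**The concern.** Two separate faults follow from one rule.

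- **Consequences admitted.** An abscess lengthens the stay, prolongs antibiotics and raises the Clavien-Dindo grade. Emergency return with IAA is the outcome itself. Such variables pass a univariate screen easily. Once in the model they take over part of the severity association that the study exists to estimate, and they make the ROC area look better than anything available when the operation ends.
- **Exposure dropped.** Irrigation is chosen by the surgeon. If dirtier cases are irrigated more often, confounding works against any benefit, and the crude comparison can look null. The gate would then remove irrigation before the adjustment that could reveal its effect.

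At stake are the adjusted severity estimate, the score weights and grades derived from it, and the adjusted irrigation estimate.

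**Working it through.** **The plan's own figure.** With "a 50% standard deviation, and a 0.03 margin of error" and z = 1.96: n = 1.96² × 0.5 × 0.5 / 0.03² = 1067.1, which reproduces 1067. It is not disputed here and only sets N. The article says "The incidence of IAA after laparoscopic appendectomy reported in the literature ranges from 1.5 to 20" per cent. At N = 1067 that is 16 events at 1.5% and 213 at 20%, with 53 at 5% and 107 at 10% in between.

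The documents give no irrigation share, no effect sizes and no stay distribution. All inputs below are therefore assumptions.

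**Step 1: a consequence of IAA enters the model.** Let stay be normal with SD s, rising by a days per grade and by b days with IAA. Let B be the true log odds ratio per grade. By Bayes' rule, the grade coefficient adjusted for stay is B − a·b/s². Take B = ln 2 = 0.693 and s = 2.

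- a = 0.5, b = 3: 0.693 − 0.375 = 0.318, odds ratio 1.37 (simulated at N = 1067: about 1.4)
- a = 0.5, b = 5: 0.693 − 0.625 = 0.068, odds ratio 1.07 (simulated: about 1.1)
- a = 1, b = 1: 0.693 − 0.25 = 0.443, odds ratio 1.56
- a = 1, b = 3: 0.693 − 0.75 = −0.057, odds ratio 0.94
- a = 1, b = 5: 0.693 − 1.25 = −0.557, odds ratio 0.57, a reversal

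For b = 1, 3 and 5 with a = 1, the simulated ROC area rises from 0.69 to 0.74, 0.88 and 0.97. If a = 0, the grade odds ratio stays at 2.0, but the ROC area still rises (to 0.88 at b = 3). So the attenuation requires that severity itself lengthens the stay; the ROC inflation does not.

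A second set of assumptions: 30% severe cases, severity odds ratio 4, log-stay SD 0.4, shifts of 0.3 for severity and 0.8 for IAA (a factor of e^0.8 = 2.2). The formula gives 1.386 − 0.8 × 0.3/0.16 = −0.114, odds ratio 0.89. In 500 simulated studies per setting, with stay entered in days, stay passed the screen every time. The severity odds ratio fell from about 4 to 0.91–0.98, severity was significant in 3–7% of runs instead of 96–100%, and the ROC area rose from 0.65–0.70 to 0.93–0.94.

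**Step 2: irrigation is screened out.** Same 30% severe and severity odds ratio 4; irrigation in 75% of severe and 25% of mild cases; risk 3% in mild cases without irrigation; true irrigation odds ratio 0.5.

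- Risks: mild 3.00% without and 1.52% with irrigation; severe 11.01% and 5.83%.
- Irrigated: (0.175 × 1.52 + 0.225 × 5.83)/0.400 = 3.94%.
- Not irrigated: (0.525 × 3.00 + 0.075 × 11.01)/0.600 = 4.00%.
- Crude odds ratio: (3.94/96.06)/(4.00/96.00) = 0.98.

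A halving of the odds disappears. In simulation, with overall IAA rates between 4% and 12.5% across the settings, irrigation was dropped in:

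- 95–96% of runs at a true odds ratio of 0.5 and 73–81% at 0.67, with this confounding;
- 15–41% and 59–72% respectively, without confounding;
- at most 1% if irrigation is harmful (odds ratio 1.5), with this confounding.

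A steeper pattern gives the same picture. With irrigation in 20/60/90% of three severity levels, risks of 2/8/20% and a true odds ratio of 0.4, irrigation passed the screen in 6–16% of runs, depending on the assumed severity mix. A severity-adjusted model recovered 0.38–0.41 with 51–71% power.

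**The case against.** **Literal reading.** Most of the postoperative list consists of outcomes, and no sentence names length of stay or Clavien-Dindo grade as a predictor. A sensible analyst would leave them out, and the *Abstract* and *Classification* describe a score built on histology and contamination. A reader might infer that the risk factors and score are bound to be wrong; the documents do not support that, because it requires mechanical application. What remains is that the written rule contains no such safeguard and the Abstract invites postoperative predictors. This is a stated rule, not a detail left to an analysis plan.

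**Stay need not rise.** Emergency returns are recorded to 90 days and rehospitalisation stay separately, so some abscesses appear after discharge. If only half (+3 days, half a day per grade, SD 2) appear before discharge, the grade odds ratio of 2.0 falls only to about 1.7. This stands: the bias shrinks but does not vanish.

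**Irrigation often survives.** Under the 20/60/90% pattern, a true odds ratio of 0.67 passes the screen in 57–84% of runs, and no effect or harm almost always passes. The masking needs a benefit that roughly cancels the confounding. This also stands.

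**The secondary endpoint has another route.** A reader might infer that losing irrigation from the model leaves the secondary endpoint unanswered. It does not: irrigation can be compared within grade by χ² whatever the screen decides. The loss is from the adjusted model. If the grades used are those derived from the score, though, that route still inherits the model's faults.

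**Histology.** Because *Conclusions* speaks of intra-operative scenarios, a reader might infer that the score must rest on the macroscopic grade alone. The article does not say the score is for use only during surgery, and it builds the classification on histology deliberately.

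**Conclusion.** The concern holds as a fault in the written rule. Followed as stated, the rule lets in variables that follow from or contain the IAA, and it makes the adjusted irrigation estimate depend on a confounded crude test.

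The directions are clear under stated conditions. The severity odds ratio is pulled toward 1, or past it, when severity also lengthens the stay. The ROC area is inflated whether or not it does. Irrigation is lost mainly when a real benefit is offset by heavier use in dirtier cases.

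The sizes are not known. For a true grade odds ratio of 2.0, plausible inputs give anything from about 1.7 to below 1. The chance of dropping a beneficial irrigation effect runs from 15% to 96% across the two-level settings examined. The documents cannot narrow either range.

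**What to change.** Replace the entry rule with a model fixed in advance:

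- Remove the p<0.05 gate and keep univariate results as description.
- Always include appendix aspect, contamination and irrigation. For the secondary endpoint, pre-specify an irrigation-by-grade interaction or estimate irrigation effects within grade.
- Limit other predictors to a short list of collected variables fixed by the operation, for example age, sex, BMI, ASA or Charlson, PIRO, CRP, operative time (cited in the Introduction as a risk factor) and operator. Keep histology as part of the classification.
- Exclude as predictors the postoperative items that follow from or contain the IAA: length of stay, ICU stay, antibiotic duration, Clavien-Dindo grade, organ/space infection and collections, emergency return with IAA, and rehospitalisation stay.
- Use penalised logistic regression if events per parameter are low. Four appendix aspects (3 contrasts), six contamination types (5), irrigation (1) and eight single-parameter covariates make 17 parameters before any interaction. That is 16/17 = 0.9 events per parameter at 1.5% incidence, 53/17 = 3.1 at 5%, 107/17 = 6.3 at 10% and 213/17 = 12.5 at 20%, so penalisation will probably be needed.

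The cost is analysis wording, with no new data. The reported ROC area will be lower and fewer predictors will be listed. With few events, the interaction will be imprecise and should be reported with its confidence intervals.

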O/S SSI must meet the following criteria:Date of event within 30 days after surgical procedurePlus involvement of any part of the body deeper than the fascial/muscle layers that are opened or manipulated during the operative procedurePlus at least one of the following:Purulent drainage from a drain that is placed into the organ/space (for example, closed suction drainage system, open drain, T-tube drain, CT-guided drainage)Organism(s) identified from fluid or tissue in the organ/space by a culture- or non-culture-based microbiologic testing method which is performed for purposes of clinical diagnosis or treatmentAn abscess or other evidence of infection involving the organ/space that is detected on the gross anatomical or histopathologic exam, or imaging test evidence suggestive of infectionPlus at least one criterion for a specific organ/space infection site listed in the CDC/NHSN Surveillance Definitions for Specific Types of Infections [7] part of 2019 Patient Safety Component Manual from Center for Disease Control and Prevention and National Healthcare Safety Network (NHSN) [8]

The average reported incidence of IAA following a laparoscopic appendectomy in the literature ranges from 1.5 to 20% with extreme heterogeneity in the types of studies considered [4, 5, 9–11].

Few studies analyzed risk factors for the development of IAA after LA. Body mass index, leukocytosis, perforated appendicitis, and operative time > 90 min were associated with the development of postoperative IAA using multivariate analysis [12–14]. A retrospective single-center analysis performed by Cho et al. with 1822 patients identified intra-abdominal irrigation as the only risk factor associated with IAA [9].

Evidence regarding advantages from peritoneal irrigation over suction only are scarce. Both guidelines from the World Society of Emergency Surgery (WSES) and from European Association for Endoscopic Surgery do not report any advantages from this practice, supported by low levels of evidence (LOE 2, GOR B) [1, 2].

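### The p < 0.05 entry rule can put lavage volume, operative time and drainage into the same model as irrigation and severity, so the adjusted odds ratios may not be the associations the endpoints name

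*Protocol article*

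**What the plan says.** All references are to the protocol article.

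- **Endpoints** (Hypothesis, design of the study, and aims). The primary endpoint is the "Relationship among each severity grade of acute appendicitis and postoperative incidence of intra-abdominal abscesses". The secondary endpoint is the impact of irrigation versus suction alone on abscess (IAA) incidence within each grade.
- **Variables** (Methods, operative data). Lavage with suction versus suction alone is recorded, as are lavage volume, drainage, operative time, operator and a difficulty grading. The Abstract widens the scope: "Preoperative, intra-operative, and postoperative predictive factors for infectious complication will also be assessed".
- **Analysis** (Data collection and statistical analysis). After chi-square tests, "univariate logistic regression will be performed to provide hazard ratios for individual variables, identifying possible predictors of postoperative complication". Then all significant "variables at univariate analysis will be included in a multivariate regression model in order to detect independent risk factors for the outcome".
- **Use of the results** (same section). For the score, "The weight of each variable will be addressed based on odds ratio values". From the ROC analysis of that score, "we will proceed to identify different severity grades of acute appendicitis each one related to a specific risk of developing delayed IAA".
- **Background** (Introduction, background, and rationale). Among the cited risk factors, "operative time > 90 min were associated with the development of postoperative IAA".

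**The concern.** The entry rule looks only at the univariate p-value. It does not separate confounders, which precede the irrigation decision, from variables that may result from the severity found or from irrigating. Two distinct problems follow.

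1. Volume is zero by definition under suction alone. A model holding both lavage yes/no and volume no longer has a coefficient that compares irrigation, as practised, with suction.
2. A severe, contaminated case plausibly takes longer and is more often drained, and lavage itself takes time. Holding time and drainage fixed removes whatever part of the severity or irrigation association runs through them.

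The secondary endpoint has the most at stake. Surgeons plausibly irrigate the worse cases, so the univariate irrigation result mixes irrigation with severity. The multivariate model is the only adjusted analysis the article states, so a reader will go to it for the irrigation effect.

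**Working it through.** **Sample size.** n = z² × p(1 − p) / e² = 1.96² × 0.25 / 0.03² = 1067.1. This reproduces the article's 1067, which is not in dispute and is used below.

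**Step 1: would such a variable pass the screen?** I took a binary operative variable present in 30–50% of patients with odds ratio 2 for IAA (both assumed), N = 1067, two-sided 5%, and the article's incidence range of 1.5 to 20%. Example at 5% incidence and 50% prevalence:
- The risks solving (p0 + p1)/2 = 0.05 with odds ratio 2 are p0 = 0.0341 and p1 = 0.0659.
- With 533.5 per group, SE = √[(0.0341 × 0.9659 + 0.0659 × 0.9341)/533.5] = 0.0133.
- The difference is 0.0318, so z = 2.39 and power is about Φ(2.39 − 1.96) = 67%.

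| IAA incidence | Events (× 1067) | Chance of p < 0.05 |
|---|---|---|
| 1.5% | 16 | 26–31% |
| 5% | 53 | 67–68% |
| 10% | 107 | 90–91% |
| 20% | 213 | 99% |

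Entry is therefore possible throughout the range and likely at mid-range incidence, but not certain.

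**Step 2: lavage and volume together.** Write logit P(IAA) = a + b·L + c·V + d·S, with L = lavage, V = volume, S = severity, and V = 0 whenever L = 0. Irrigating with volume v versus suction alone, at equal severity, has log odds ratio b + c·v. So b alone is the value at v = 0, which no irrigated patient has. This is algebra and needs no clinical assumption.

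L and V are also correlated by construction. If a fraction q is irrigated, with mean volume m and SD s among them, r² = (1 − q)m² / [s² + (1 − q)m²]. The variance inflation for b is then about 1 + (1 − q)(m/s)² (linear approximation). With q = 0.5 assumed:
- s/m = 0.4 gives 1 + 0.5/0.16 = 4.1, so the SE is multiplied by 2.0.
- s/m = 1.0 gives 1 + 0.5/1 = 1.5, so the SE is multiplied by 1.2.

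**Step 3: illustration.** Every parameter here is assumed.
- 35% of cases are severe.
- Lavage log-odds are −0.4 + 1.2·severe.
- Volume if irrigated has mean 1.0 + 0.6·severe litres and SD 0.4.
- Standardised operative time is 0.7·severe + 0.5·lavage plus noise of SD 0.8.
- Drain log-odds are −1.5 + 1.5·severe + 0.5·lavage.
- IAA log-odds are −4.2 + 0.5·severe + 0.1·lavage + 0.5·time + 0.4·drain + 0.3·volume, which gives IAA in 4.5%.

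Odds ratios come from 1,000,000 simulated patients. Standard errors are medians over 300 samples of 1067.

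| Model | Severity OR | Lavage OR | SE of lavage log-OR |
|---|---|---|---|
| Severity alone | 3.68 | – | – |
| Lavage alone | – | 2.92 | – |
| Severity + lavage | 3.01 | 2.16 | 0.350 |
| … + volume | 2.65 | 1.43 | 0.666 (×1.90) |
| … + time + drain | 1.86 | 1.62 | 0.369 (×1.05) |
| … + volume + time + drain | 1.63 | 1.07 | 0.679 (×1.94) |

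Volume passed the univariate screen in 99% of samples, time in about 100% and drain in 83%.

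Three things are visible. Crude lavage (2.92) overstates the severity-adjusted figure (2.16), which is the confounding. Nearly all the loss of precision comes from volume. Time and drain mainly move the severity odds ratio.

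**The case against.** **Entry is conditional.** The article names no covariates, and a candidate list may sit in the full plan. At the lowest incidence an odds-ratio-2 variable would more often miss the screen than pass it. This stands: the rule *can* admit these variables, and a reader should not infer that the model will adjust for them.

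**The model is not named as the endpoint estimator.** Its stated purpose is to find independent risk factors and feed the score. The chi-square and univariate analyses still give the crude severity–IAA relationship, which is close to the primary endpoint as worded. The article also speaks of clustering patients by grade, lavage and IAA, which hints at comparisons within grade. This stands for the primary endpoint. For irrigation it stands only in part: no within-grade analysis is actually stated, and the crude result is confounded.

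**A predictive score may use intra-operative items.** Weights conditional on the other predictors are then correct. A reader might infer that severity is wrongly underweighted in the score, but the documents do not support that: risk carried by a drain or a long operation would be scored under those items. What remains is that such weights are not severity or irrigation effects.

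**The causal order is inferred.** Nothing in the article says that drainage or operative time follow from severity or lavage. Time may also reflect the operator or body build. That inference is plausible rather than documented. The point about volume does not depend on it.

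**The illustration is built to show attenuation.** The full model recovers roughly the direct effects that were put in. This stands, so the figures show direction and mechanism only.

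**Conclusion.** The point holds in conditional form. As written, the screen has no safeguard against placing lavage volume, operative time and drainage in the same model as irrigation and severity.

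The volume problem is definitional: with both terms in, the lavage coefficient refers to 0 mL and loses precision. The time and drainage problem rests on the plausible assumption that they partly follow from severity or irrigation. If they do, the adjusted odds ratios are not the total associations named in the endpoints. The secondary endpoint is affected most.

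No amount of attenuation can be derived from the document. The illustrative shifts (lavage 2.16 to 1.43 with volume; severity 3.01 to 1.86 with time and drainage) depend wholly on the assumed parameters and on the downstream effects acting in the same direction. A reader might go further and expect a real irrigation effect to be reported as absent. That is possible under such assumptions, but the documents do not show it.

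**What to change.** For the endpoint analyses, replace the p < 0.05 screen with pre-specified models:

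- **Irrigation (secondary endpoint):** lavage, severity grade, a lavage-by-grade term or grade-specific estimates, a named set of pre-operative variables, and operator. Leave out lavage volume, operative time and drainage. A single pooled lavage odds ratio would not answer an endpoint worded for each grade.
- **Severity (primary endpoint):** report the association without those three variables. Decide in advance which pre-operative variables enter, since CRP, Alvarado and PIRO may themselves reflect severity.
- **Lavage volume:** analyse it only among irrigated patients.
- **Score:** if it is meant to predict, intra-operative items may stay. State that its weights are not severity or irrigation effects, and do not enter lavage and volume as separate terms.

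This changes analysis wording only and needs no new data or sample size. The cost is slightly more analysis and one extra model to report. Grade-specific lavage estimates will be imprecise if incidence is near the low end (about 16 events at 1.5%), and the report should say so.

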Appendix aspect	
Erythematous and edematous appendix^a^	
Appendiceal phlegmon^b^	
Gangrenous appendix^c^	
Perforated appendix^d^	
Contamination	
Single abscess	
Multiple abscesses	
Localized purulent peritonitis	
Diffuse purulent peritonitis	
Localized fecal peritonitis	
Diffuse fecal peritonitis	

^a^Neutrophils within mucosa and submucosa with mucosal

^b^Neutrophilic infiltration of mucosa, submucosa, and muscolaris propria. Transmural inflammation, extensive ulceration, and intramural abscess; vascular thrombosis

^c^Transmural inflammation with areas of necrosis; extensive mucosal ulceration

^d^Transmural inflammation with areas of necrosis; extensive mucosal ulceration plus parietal disruption [17]

One type of appendix aspect will be assigned to each patient, as well as one type of contamination will correspond to a single patient.

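### If the abscess rate is below about 10%, 1067 patients give too few events for the planned odds-ratio score, which will be overfitted without shrinkage

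*Protocol article*

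**What the plan says.** The protocol article, under Data collection and statistical analysis, sizes the study from a single-proportion precision formula, "given a 95% confidence interval with a *z*-score of 1.96, a 50% standard deviation, and a 0.03 margin of error", and adds: "This formula does not include the incidence rate of IAA for the aforementioned reasons". The result is stated as "The estimated sample size would be around at least 1067 patients". The same section notes that "The incidence of IAA after laparoscopic appendectomy reported in the literature ranges from 1.5 to 20" per cent.

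Table 1 (Classification) lists four appendix aspects and six contamination types. Each patient receives one of each: "One type of appendix aspect will be assigned to each patient, as well as one type of contamination will correspond to a single patient". Methods lists baseline and operative variables that are also available as predictors.

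For the model, all significant "variables at univariate analysis will be included in a multivariate regression model in order to detect independent risk factors". The score follows from it: "The weight of each variable will be addressed based on odds ratio values". Discrimination is then judged by ROC analysis and calibration by the Hosmer-Lemeshow test, and severity grades are drawn from the ROC results. The section gives no expected number of abscesses, no limit on model size and no shrinkage.

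**The concern.** A logistic model for a binary outcome is limited by the number of events, not the number of patients. The protocol treats the wide IAA range as a reason to leave the rate out of the sizing, but the number of events still depends on that rate. In the lower half of the range there are few abscesses per parameter.

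Selecting on p < 0.05 and then reading weights directly from the fitted odds ratios keeps the most extreme chance estimates. Predicted risks in new patients are then too spread out, and the ROC area in the development data flatters the score. A rare severe grade that happens to have no abscess gets an odds ratio of 0 and would score as protective.

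The Discussion calls classifying patients and creating the score the core step, and the Conclusions offer the score to emergency surgeons, so distorted weights reach the study's main product.

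**Working it through.** **1. The protocol's figure.** n = z² p(1−p)/d² with z = 1.96, p = 0.5 (reading the 50% standard deviation as p = 0.5) and d = 0.03: 1.96² × 0.25 / 0.03² = 1067.1. The stated 1067 is reproduced.

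**2. Parameters.**
- Classification: 4 aspects need 3 parameters and 6 contamination types need 5, so 8 in all, or 9 if a level for no contamination is added.
- Other variables in Methods, at one parameter each: 8 baseline (age, sex, BMI, ASA, Charlson, PIRO, Alvarado, CRP) and 6 operative (lavage or suction, lavage volume, drainage, operative time, operator, difficulty).
- Upper case: 9 + 14 = 23.

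**3. Events and events per parameter.** Events = 1067 × rate.

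| IAA rate | Events | Per parameter, 9 | Per parameter, 23 (upper case) |
|---|---|---|---|
| 1.5% | 16 | 1.8 | 0.7 |
| 5% | 53 | 5.9 | 2.3 |
| 10% | 107 | 11.9 | 4.6 |
| 20% | 213 | 23.7 | 9.3 |

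The common benchmark of 10 events per parameter needs 90 events for 9 parameters, a rate of 90/1067 = 8.4%. For 23 parameters it needs 230 events, 230/1067 = 21.6%, just above the quoted range.

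**4. Sample size for limited shrinkage.** n = P / [(S−1) ln(1 − R²/S)], with S = 0.9, P = 9 and R² set to 15% of its maximum (an assumption). At 10% the maximum is 1 − exp[2(0.1 ln 0.1 + 0.9 ln 0.9)] = 0.478, so R² = 0.0717 and n = 9 / (0.1 × 0.0830) ≈ 1084. The corresponding n is 3699 at 1.5%, 1603 at 5% and 809 at 20%. On this assumption 1067 is about right for the classification alone at 10%, and short below that.

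**5. The planned selection, simulated.** The documents give no grade frequencies; they say that "the incidence of intra-abdominal abscesses has never been systematically investigated in regard to the severity of appendicitis and contamination". The inputs below are therefore assumptions:
- N = 1067; aspects 30/40/18/12%.
- Contamination: none 55%, single abscess 8%, multiple 2%, localized purulent 20%, diffuse purulent 10%, localized fecal 3%, diffuse fecal 2%.
- Log-odds 0 to 1.2 by aspect and 0 to 1.4 by contamination; irrigation in 50%; 12 further covariates, 3 of them predictive.
- Only variables with univariate p < 0.05 enter. Effect sizes were varied, including a doubling of the log-odds.

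| IAA rate | Calibration slope in new patients (ideal 1) |
|---|---|
| 1.5% | about 0.2 |
| 3% | 0.4–0.7 |
| 5% | 0.6–0.8 |
| 10% | 0.7–0.9 |
| 20% | 0.8–0.9 |

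At 5%, apparent versus true ROC area was 0.71 vs 0.62, and 0.85 vs 0.81 with stronger effects.

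**6. Grades without an event.** P(no abscess among m patients) = (1−r)^m, where r is the rate within the grade. For m = 20 this is 74% at r = 1.5%, 36% at 5%, 12% at 10% and 1% at 20%. In 1000 simulated cohorts per rate, with a similar set of assumed shares (rarest types 2–3%), at least one level had no event in 86% at 1.5%, 50% at 3%, 19% at 5%, 1.6% at 10% and 0% at 20%. With the planned selection applied to the shares in step 5, a classification factor with an empty level still entered the score model in 25%, 20%, 11% and 4.5% of cohorts at 1.5, 3, 5 and 10%.

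**The case against.** - **The shortage does not cover the whole range.** A reader might infer that 1067 is too few anywhere between 1.5 and 20%. The figures do not support that. From about 8.4% the classification alone meets the benchmark of 10 events per parameter, and at 20% even the 23-parameter model comes close. 1067 is also a stated minimum.
- **The full list of variables is not the planned model.** Only significant variables enter. In one run with selection, the median number of parameters entering was 2 at 1.5%, 7 at 5%, 11 at 10% and 12 at 20%. Overfitting is milder than in an all-variables fit, but it remains, because selection itself uses up the same few events.
- **Infinite odds ratios are not the usual result.** A reader might expect empty grades to produce them. An empty non-reference grade gives an odds ratio of 0; an infinite one needs an empty reference grade. With the base effect sizes the reference was empty in about 4% of runs at 1.5% and in none from 3% up. The usual error for an empty severe grade is a weight that is too low.
- **The simulated sizes rest on assumptions.** Grade shares and effects are not in the documents, and stronger effects give better slopes. This stands, and is why ranges are shown.
- **Silence is not refusal.** The protocol does not reject penalisation, and an unseen analysis plan may add it. The point therefore rests on what the protocol does fix: entry by p < 0.05, weights from odds ratios, and a sample size that ignores the event rate.

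**Conclusion.** The point holds for IAA rates below about 10%, which lie within the protocol's own range. There, 16 to 107 abscesses support 8–9 classification parameters at about 2 to 12 events each, and fewer when covariates enter. Following the plan as written would give an overfitted score with an optimistic ROC area: severely so at 1.5–3%, materially at 5%, moderately at 10% and mildly at 20%.

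The event counts follow from the protocol's figures alone. The slopes, ROC areas and empty-grade frequencies depend on assumed grade shares and effect sizes. The documents do not show that the score must fail at every rate, or that infinite odds ratios are to be expected.

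**What to change.** In Data collection and statistical analysis, where the model and score are described:

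- Fit the score model with penalisation: Firth for the reported odds ratios; for the score, ridge with a tuned penalty, or bootstrap shrinkage that repeats the variable selection in every resample.
- Derive points from the shrunken log-odds coefficients.
- Report the bootstrap optimism-corrected ROC area and calibration slope.
- Before outcomes are seen, merge sparse contamination types by a pre-set rule based on expected events in the type (patients in the type × an assumed rate). A fixed threshold of 20 patients would miss the problem: a 2% type expects 1067 × 0.02 = 21 patients (and about 1 abscess at a 5% rate), and falls below 20 with probability 35%; a 3% type expects 32 and does so with probability under 1%.
- Name the merging partner for every type: single with multiple abscesses, localized with diffuse purulent, localized with diffuse fecal.

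Where the sample size is given, state that 1067 patients are expected to yield 16 to 213 abscesses and that at the lowest rates the score would be exploratory. Penalisation limits the damage but cannot supply missing events.

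The cost is wording and modest programming, with no extra patients required. The downside is shrunken weights, a less favourable ROC area and possibly a coarser classification.
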